### Assessment of outcomes

All assessment sessions (baseline [time 1], 1 month [time 2], 3 months [time 3], and 6 months [time 4] postsurgery) include measurement of the primary and secondary outcomes. A series of questionnaires related to health outcomes of the SEEI is implemented. During the baseline assessment, additional demographic information including health, medical history, and general health status is collected.

#### Primary outcomes

##### Self-efficacy for rehabilitation (SER) outcome scale

The 12-item SER was developed by Waldrop et al. [28], following Bandura’s guidelines [34] to assess participant beliefs about their ability to perform behaviors typical in physical rehabilitation for knee and hip surgery. The SER was developed in conjunction with rehabilitation psychologists and physical and occupational therapists. Items increase in difficulty (e.g., items assessing self-belief in ability to stretch a leg, to those assessing beliefs in one’s ability to walk). Items measure belief in ability to perform behaviors in varying therapy situations, including when experiencing pain and emotional distress. For each item, participants use an 11-point Likert scale, ranging from 0 (I cannot do) to 10 (certain I can do) to describe their confidence. The full score for the items is 120, and higher scores indicate more perceived self-efficacy for rehabilitation. According to Bandura [34], “efficacy scores are summed and then divided by the total number of items to indicate the strength of perceived self-efficacy for the activity domain.” Thus, mean self-efficacy scores were calculated. In this study, the reliability and validity of the Chinese version SER outcome scale will be assessed by six orthopedic nurses. The Cronbach’s alpha reliability coefficient value for the total scale was 0.942.

##### Functional exercise compliance scale for THA patients

The self-designed exercise compliance questionnaire was developed by Xinxin Li of Sun Yat-sen University [30]. It can be divided into three dimensions: physical exercise compliance, exercise monitoring compliance, and initiative-seeking advice compliance. Each item is rated on a 4-point scale (4 points = “always do,” 3 points = “almost always do,” 2 points = “occasionally do,” and 1 point = “never do”). The sum of item scores is the total score, with higher total scores indicating a greater level of compliance level with functional exercise. In this study, Cronbach’s alpha ranges from 0.915 to 0.947, with an intra-rater reliability value of 0.92.

#### Secondary outcome measures

##### Overall hip pain

Average overall hip pain in the past week is self-assessed using an 11-point numeric rating scale with score 0 representing “no pain” and 10 representing “extreme pain” (e.g., “pain as bad as you can imagine” or “worst pain imaginable”) [40–42]. Participants select the whole number (0–10) that best reflects the intensity of their pain.

##### Activity and participation (WHO-DAS II)

The World Health Organization Disability Assessment Schedule II (WHO-DAS II) was developed building on the theoretical models described and recommended by the 2001 International Classification of Functioning, Disability and Health, regarding the general evaluation and measurement of health conditions, disabilities, and psychometric variables [43]. The WHO-DAS II provides a standardized cross-cultural method for measuring the health and disability status of adults (aged over 18 years) over a 30-day period and contains 32 items covering six domains: cognition, mobility, self-care, getting along with people, activities of daily life, and social participation [44]. Scores are classified into five levels: no difficulty, mild difficulty, moderate difficulty, severe difficulty, and extreme difficulty [45]. The total score range is 0–100, with higher scores indicating higher limitations in daily life. In this study, the reliability of Cronbach’s alpha and intraclass correlation coefficient in the WHO-DAS II are 0.73–0.99 and 0.8–089, respectively, illustrating that the Chinese version is suitable to assess activity and participation [46].

##### Anxiety and depression

Anxiety and depression are measured using the Chinese version of the Hospital Anxiety and Depression Scale (C-HADS) [47]. The HADS is a self-report questionnaire designed to assess depression and anxiety and has been widely used among patient groups [48]. This instrument consists of 14 items (7 for anxiety [HAD-A] and 7 for depression [HAD-D]), which are used as two separate measures of psychological disturbance. Each subscale is scored from 0 to 21, with higher scores indicating greater distress. The psychometric properties of C-HADS have been confirmed, with satisfactory results in terms of reliability and validity [47]. In this study, the Cronbach’s alpha reliability coefficients for both the anxiety and depression subscales are both 0.85 [49].

##### Hip function

Hip function is monitored using the Harris Hip Score (HHS) for hip arthroplasty, a multidimensional disease-specific observational assessment of functioning, containing eight items representing pain, walking function, activities of daily living, and range of motion of the hip joint [50]. The HHS is widely used by physicians to assess physical function and pain relief in patients with hip disease [51]. The maximum score for the HHS is 100 points, with maximum possible scores for its components as follows: pain (44 points), function (47 points), range of motion (5 points), and deformity (4 points) [52]. A higher HHS score indicates better function.

##### QOL

Physical and mental health are assessed using the 12-item Short Form Health Survey (SF-12), a validated measure of QOL following joint replacement [53]. The SF-12 comprises 12 items for assessing physical and mental health and yields two summary scores: the physical and mental health composite scores [53, 54]. Scoring is norm-based, with a mean of 50 (SD = 10); lower SF-12 scores indicate poorer physical and/or mental health. The Chinese versions of SF-12 components are established as reliable and valid in older patients [55].

### Sample size, statistical analysis, and monitoring

#### Sample size calculation

The required sample size was determined as 64 patients in each group based on a previous study [56]. The study that our sample size calculations are based on experienced a low withdrawal rate (10%). We have made a conservative estimate of a 15% withdrawal rate; therefore, we intend to recruit 150 participants.

### Randomization and blinding

After completing all baseline data collection measures, participants are randomly divided into the intervention and control groups using computer-generated random numbers. Participants are assigned a series of continuous integers in the order of admission. To hide randomization, the independent researcher has prepared consecutively numbered, sealed, opaque envelopes, which are kept in a locked location. To avoid affecting exercise adherence behavior, participants are not informed of the two separate studies, re-randomization into this trial, or the exact details of the intervention. This process ensures adequate concealment, limiting the possibility of selection deviation. The statistician will be blinded to group allocation, which will be revealed upon completion of the statistical analyses.

### Data analysis

IBM SPSS 25.0 will be used to analyze the collected data, according to the intent-to-treat principle. An alpha level of 0.05 will be applied for all statistical tests, and a 95% confidence interval used for all estimated values. Missing data will be managed using the last-observation-carried-forward method; this imputation method replaces missing values in the post-baseline follow-up with the last observed value for each individual. Descriptive statistics and frequency distributions will be generated for patient demographic and disease-related characteristics. Independent *t* tests and *χ*^2^ analyses will be performed to evaluate whether there are significant differences in demographic or clinical characteristics and baseline measures between the control and intervention groups. A repeated measures multivariate analysis of variance will be used to test the effects of group assignments (intervention vs. control), time (pretest vs. posttests), and group by time interaction, for the four outcome measures. If the assumption of sphericity is not met, the degrees of freedom for the *F* ratio will be adjusted according to Greenhouse-Gessler epsilon. *P*-values < 0.05 will be considered statistically significant for all comparisons.

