A number of studies have shown that enhancing self-efficacy is helpful to patient self-management and promotes health-related behaviors and good outcomes. Related interventions have been successfully applied in people with coronary heart disease [22], diabetes [23], hypertension [24], stroke [25], arthritis [26], and joint replacement rehabilitation [27, 28]. Therefore, patients should believe in their ability to perform specific physical activities to improve their rehabiliation after THA. Previous investigations have shown moderate self-efficacy of Chinese patients after hip and knee arthroplasty [29, 30]. Nevertheless, studies in this field are scarce, the majority used small sample sizes, and self-efficacy has not been considered in rehabilitation program development, leading to substantial extension of rehabilitation times and unsatisfactory outcomes.

The theory of self-efficacy provides a good basis for nursing interventions for patients after THA. This study is inspired by the self-efficacy theory of Bandura, which proposes that enhancement of self-efficacy is beneficial for patient rehabilitation and for achieving optimal outcomes. To investigate this further, we developed a 6-month self-efficacy-enhancing intervention (SEEI), to support adherence to prescribed home-based exercise for patients following THA. The SEEI was developed in rigorous accordance with Bandura’s self-efficacy theory and is a complex intervention. That theory is here applied to rehabilitation after THA.

Our primary hypothesis is that adherence to the prescribed home exercise program in the 6 months after THA will be higher in the group receiving the SEEI compared with the group receiving usual care. Our second hypothesis is that the SEEI group will exhibit greater improvements in other outcomes (e.g., pain, function, health-related quality of life [QOL], anxiety and depression, and another measure of exercise adherence) than the control group.

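### The primary hypothesis names adherence only, but two outcomes are listed as primary, every test uses 0.05, and neither a success rule nor a deciding effect is stated

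*Protocol article*

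**What the plan says.** All references are to the protocol article.

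- **Hypothesis (Background).** "Our primary hypothesis is that adherence to the prescribed home exercise program in the 6 months after THA will be higher" in the intervention group. The second hypothesis gives examples of other outcomes, and self-efficacy is not among them.
- **Primary outcomes (Assessment of outcomes).** Two scales stand under this heading. The first is the "Self-efficacy for rehabilitation (SER) outcome scale", on which "higher scores indicate more perceived self-efficacy for rehabilitation". The second is the functional exercise compliance scale, for which "The sum of item scores is the total score". Five secondary headings follow: pain, WHO-DAS II, anxiety and depression, Harris Hip Score and SF-12.
- **Visits (Assessment of outcomes).** Baseline and 1, 3 and 6 months after surgery. None is named as primary.
- **Tests (Data analysis).** A repeated measures multivariate analysis of variance tests group, time and "group by time interaction, for the four outcome measures". The significance rule appears twice: "An alpha level of 0.05 will be applied for all statistical tests", and p-values below 0.05 "will be considered statistically significant for all comparisons".

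**The concern.** The hypothesis, the outcome list and the analysis describe three different primary questions. The hypothesis has one outcome, the outcome section has two, and the analysis has four unnamed ones. Four fits neither the two primary scales, nor the six indicators in the abstract's Results paragraph, nor the seven instruments described under Assessment of outcomes.

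Two decisions are left open: whether one or both primaries must succeed, and whether the group effect or the group-by-time effect settles the matter. Each open decision lets the choice be made after the results are seen.

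The pairing also matters for interpretation. Self-efficacy is what the coaching is designed to raise (Intervention theoretical framework), and adherence is what raising it is supposed to change. A real effect on self-efficacy with none on adherence would meet a listed primary outcome while leaving the primary hypothesis unsupported. That risk exists even where no false positive occurs.

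**Working it through.** **Inputs from the article.** Alpha is 0.05 per test with no adjustment (Data analysis). There are two primary outcomes, two between-group effects (group, and group by time) and four visits. The sample size is 64 per group, with 15% withdrawal and 150 recruited (Sample size calculation).

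**Assumptions, not in the article.** Tests are two-sided, in line with "a 95% confidence interval used for all estimated values". Correlation between the two outcomes is varied from 0 to 0.9. Within-person correlation between visits is 0.5 or 0.7. The effect size behind 64 per group is not given. A standardised difference of 0.5 is used below because it reproduces 64.

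**The plan's own figure.** 2 × 64 = 128, and 128 / 0.85 = 150.6, so 151. By the alternative convention, 128 × 1.15 = 147.2, so 148. Both agree with 150 within rounding. At a difference of 0.5 SD, a two-sample t test at two-sided 0.05 with 80% power needs 63.8, so 64 per group (power 80.1%). On that assumption, 64 is the size for one test at the full 5%.

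**Case A: success on either primary, one named effect each.** The upper bound is 2 × 0.05 = 10%. With independent tests, 1 − 0.95² = 9.75%. With correlated test statistics, the rate is 1 − P(|Z₁| ≤ 1.96 and |Z₂| ≤ 1.96) under a bivariate normal distribution:

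| Correlation | 0 | 0.3 | 0.5 | 0.7 | 0.8 | 0.9 |
|---|---|---|---|---|---|---|
| At least one false positive | 9.75% | 9.5% | 9.1% | 8.3% | 7.8% | 7.0% |

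**Case B: adherence alone, either the group or the interaction effect counts.** The group test uses each patient's mean over visits, and the interaction uses deviations from that mean, so the two are close to independent: 1 − 0.95² = 9.75%. A null simulation (64 per group, four visits, 20,000 runs per setting) gave 9.6% to 10.0%.

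**Case C: either primary and either effect counts.** With four independent tests, 1 − 0.95⁴ = 18.5%. The simulation gave 13.8% to 18.9% as the correlation between outcomes went from 0.9 to 0.

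**Case D: both primaries must succeed, one named effect each.** At most 5%.

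**Case E: adherence as sole primary with one named effect.** 5%, and 64 per group stands.

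**Cost of splitting alpha instead.** At 0.025 per outcome, family-wise error is 1 − 0.975² = 4.94% if independent. Under the assumed 0.5 SD, power per outcome at 64 per group falls from 80.1% to 71.2%. Restoring 80% needs 78 per group: 156 / 0.85 = 183.5, so 184 recruited rather than 150.

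**The case against.** **No success rule is stated, so no inflation is shown.** This is correct as far as it goes. The Study design section hypothesises benefit on self-efficacy and compliance together, and if both are required the error is at most 5% (Case D). What can be shown is that the rule is missing and that the error ranges from 5% to about 18.5% depending on it.

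**Hierarchy and multiplicity belong in the analysis plan.** That would answer a silent protocol. This one is not silent: it applies 0.05 to all tests and all comparisons, so an analysis plan that adjusted would contradict it. The mismatch between hypothesis and primary outcomes also lies within the article itself.

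**The analysis is multivariate.** A single joint test of one effect would hold 5% under the global null. However, the section adjusts the F ratio for non-sphericity, which is a univariate repeated-measures step and suggests outcome-by-outcome tests. A joint test would also not show that adherence in particular improved.

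**Stronger readings that the document does not support.** A reader might infer that the trial's main claim carries a false-positive rate of 10% or more because self-efficacy is also tested. If the main claim is adherence, the self-efficacy test does not inflate its error. Case A concerns benefit on at least one primary, and there 10% is a ceiling, not a floor. A reader might also infer that having no primary visit multiplies the tests by three. The article states no visit-by-visit tests, and a repeated-measures analysis over the six months uses all visits together. The gap is the unnamed deciding effect.

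**It is a pilot.** The abstract uses that word, but Background, Study design and Discussion state hypotheses about effectiveness, so error control is relevant.

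**Conclusion.** The point holds as an internal contradiction combined with a blanket 0.05 rule. The hypothesis names one outcome, two are listed as primary, the analysis covers four unidentified measures, and nothing says which effect or which combination decides.

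The false-positive rate is 5% for adherence alone on one named effect. It is about 10% for adherence alone if either effect may count, and up to about 10% if either primary suffices on one named effect. It reaches up to about 18.5% if either primary and either effect may count, and that top figure requires four independent tests. These rates assume two-sided tests. The lower values rest on assumed correlations; the direction of correlation is the one the protocol's theory implies, but its size is unknown. That the trial could be declared positive on self-efficacy alone is something the text permits, not something it states.

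**What to change.** Before any unblinded analysis, and reported as a change because the Discussion describes the trial as ongoing:

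1. Make the compliance score the single primary outcome. State that it is the total score or, if intended, the physical exercise dimension, since the scale also scores monitoring and advice-seeking.
2. Name one between-group contrast from the repeated-measures model, tested at two-sided 0.05. The average over the 1-, 3- and 6-month visits fits a hypothesis about the whole six months. The month 6 difference is an alternative. Other effects from the model become supportive.
3. Test self-efficacy second in a fixed sequence at 0.05, only if the compliance contrast is significant, or list it as secondary.
4. Replace the reference to four outcome measures with the actual list.

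The cost is a protocol amendment, a registry update and a note in the report. The sample size does not change, whereas splitting alpha would lose power or need more patients. The real downside is that self-efficacy alone can no longer make the trial positive.

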## Background

Total hip arthroplasty (THA) is a major surgical procedure performed worldwide [1]. Approximately 400,000 THAs are performed annually in China [2], and this is growing rapidly due to the high level of patient needs and the challenges of an aging population [3, 4]. THA is a cost-effective intervention that reduces or even eliminates pain [5]. Despite these encouraging facts, differences remain in patient self-reported functional improvement after THA [6, 7]. Some studies have reported significant positive correlations between the surgical effects in patients after hip/knee arthroplasty and exercise adherence [8–11]. Exercise adherence is indeed a fundamental determinant to the success of hip arthroplasty, as plenty of new technologies and integrated pathways aim to enhance [12]. Home exercise adherence is usually high in the early stage but gradually decreases over time [13, 14]. As poor adherence to home exercise is common and affects therapeutic effectiveness and healthcare costs [15], there is an urgent need for economic, achievable, and effective interventions to improve home exercise adherence [16].

Self-efficacy is an important part of promoting healthy behavior and a significant determinant influencing the initiation and maintenance of positive health behaviors [17, 18]. The concept of self-efficacy was first proposed in 1977 [19]. According to self-efficacy theory, if individuals believe that they can achieve results, then they become more active and in control of their lives. A high sense of individual self-efficacy can lead to positive health behaviors [19, 20]. A higher sense of self-efficacy indicates that individuals will exhibit good exercise adherence, while a lower sense of self-efficacy is regarded as an obstacle to ensuring effective rehabilitation [21].

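### LOCF is the only missing-data method although neither adherence nor function is expected to stay flat, so the 6-month comparison is liable to bias that depends on dropout by arm

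*Protocol article*

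**What the plan says.** Under Data analysis, the protocol article sets an intent-to-treat analysis in SPSS 25.0 by repeated measures multivariate analysis of variance, with group, time and their interaction. For gaps in the data it states "Missing data will be managed using the last-observation-carried-forward method" and explains that "this imputation method replaces missing values in the post-baseline follow-up with the last observed value for each individual". As worded, a patient with no follow-up visit is carried forward at the baseline value.

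Scores are collected at "baseline [time 1], 1 month [time 2], 3 months [time 3], and 6 months [time 4] postsurgery". The main claim to be tested, with usual care as the comparator, reads: "adherence to the prescribed home exercise program in the 6 months after THA will be higher in the group receiving the SEEI". The functional exercise compliance scale is listed as a primary outcome.

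On the expected course, the Background says: "Home exercise adherence is usually high in the early stage but gradually decreases over time". It also describes THA as reducing or removing pain, and the Abstract links rehabilitation to better joint function.

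On loss, the Sample size calculation says: "We have made a conservative estimate of a 15% withdrawal rate; therefore, we intend to recruit 150 participants". No split by arm or visit is given. Under Development of the SEEI program, a WeChat account intended partly to limit loss to follow-up is set up for the experimental group only.

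**The concern.** LOCF is neutral for a patient mean only if scores stay level after the last visit. The article's own account points away from that in two directions: adherence drifts down, while pain and function recover. A patient last seen at month 1 would on average receive too high a 6-month adherence score and too low a 6-month function score.

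Errors of this kind cancel between arms if both lose patients equally and follow parallel courses. Two features of this trial make cancellation doubtful. First, a retention aid in one arm makes unequal loss foreseeable, most likely with more loss in control. Second, if SEEI works by sustaining adherence, the arms separate over time, and LOCF then pulls the 6-month difference back towards its earlier, smaller value even when loss is equal. At stake are the adherence estimate on which the primary hypothesis rests and the credibility of any functional benefit.

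**Working it through.** **Planned loss.** "The required sample size was determined as 64 patients in each group based on a previous study" gives 128 in total. 128 / 0.85 = 150.6, which agrees with the stated 150. At 15%, 0.15 × 150 = 22.5 patients are lost, so about 22 would have imputed 6-month scores.

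**Inputs that must be assumed.** The article gives no trajectory, SD or loss by arm. Scores are in SD units with 75 per arm. Adherence declines linearly by D = 0.5 or 1.0 SD from month 1 to month 6. Everyone has a month 1 score, and dropouts are split evenly between last seen at month 1 and last seen at month 3. Tests are two-sided at 0.05. Differences are SEEI minus control.

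**Formula.** With shares d1 and d2 last seen at months 1 and 3, the LOCF mean at month 6 is (1 − d1 − d2)·m6 + d1·m1 + d2·m3. Under a linear decline, m1 = 0, m3 = −0.4D and m6 = −D. With total loss d split evenly, the arm's error is d/2·D + d/2·0.6D = 0.8·d·D.

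**Adherence, no true effect.**
- Loss 10% SEEI, 20% control: 0.8·D·(0.10 − 0.20) = −0.08·D, that is −0.04 SD (D = 0.5) or −0.08 SD (D = 1.0), against SEEI.
- The standard error is √(2/75) = 0.163, so the shift is 0.245 or 0.490 standard errors. Two-sided type I error is 5.7% or 7.8%.
- Equal loss: the errors cancel and type I error is 5.0%.

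**Adherence, true 6-month effect of 0.50 SD.**
- Growing effect (control falls D, SEEI falls D − 0.5), 15% loss in both arms: 0.8 × 0.15 × (−0.5) = −0.06, so LOCF expects 0.44, 12% too small.
- Growing effect, loss 10% SEEI and 20% control: 0.42 (D = 0.5) or 0.38 (D = 1.0).
- Growing effect, loss 20% SEEI and 10% control: 0.46 or 0.50.
- Constant effect (parallel decline), equal loss: 0.50, no bias.
- Power with equal loss and a growing effect: at 0.44 with 75 per arm, 0.44/0.163 − 1.96 = 0.73, giving 76.9%. For the 64 completers per arm, 0.50/√(2/64) − 1.96 = 0.87, giving about 81%. The cost is about 4 percentage points.

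**Function, no true effect.** Assume a total gain G of 2 to 3 SD, reached 50%, 80% and 100% at months 1, 3 and 6. The bias is G × (mean share of the gain still to come) × (control loss − SEEI loss). With 20% against 10% loss:
- Last seen at month 1 or 3: mean share (0.5 + 0.2)/2 = 0.35. Bias is 0.07 (G = 2) to 0.105 SD (G = 3), favouring SEEI.
- Last seen at baseline, month 1 or month 3: mean share (1.0 + 0.5 + 0.2)/3 = 0.567. Bias is 0.11 to 0.17 SD.
- Simulation (4,000 replicates, correlation 0.5, 6-month t test) under this and similar recovery paths reached 0.18 SD. Type I error was about 6 to 10% if nobody was lost before month 1, and about 10 to 14% if some were.

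**Check of the alternative.** In a simulation of 3,000 trials with correlation 0.6 and dropout depending on the last observed adherence score, an analysis valid under missing at random averaged 0.497 to 0.501 for a true 0.50 with about 15% loss per arm. LOCF averaged 0.438 to 0.443. With no effect and about 10% against 19% loss, the averages were −0.001 to 0.002 and −0.017 to −0.049 respectively.

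**The case against.** Much of the opposing case stands.

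- A reader might infer that dropouts are fixed at values known to be wrong and that the comparison is certainly biased. The Background sentence is general, gives no size and concerns exercise adherence. It does not cover self-efficacy, the other primary outcome, and the compliance scale also covers monitoring and advice-seeking. With parallel courses and equal loss the difference is unbiased.
- On adherence, the one documentary ground for unequal loss (WeChat for SEEI) points to more loss in control, and the bias then runs against SEEI. False claims of SEEI benefit become rarer. The larger inflation concerns function, which is secondary, and needs assumed gains of 2 to 3 SD.
- More extreme splits, such as 25% against 5%, give much larger errors but have no basis in the article, which gives 15% overall. They are not relied on here.
- These figures come from a 6-month t test, not the planned analysis. A multivariate group-by-time test on LOCF adherence data at 20% against 10% loss rejected only 5.2 to 6.3% of the time.
- A reader might add that LOCF makes the standard errors wrong. LOCF does treat imputed scores as observed, but with equal loss and no effect the t test rejected 4.5 to 5.3% of the time, so no practical harm was shown.
- A missing sensitivity analysis is no finding, since an analysis plan that is not shown may hold it.

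What the objection does not remove is that the article fixes LOCF as the method, and that its flat-course assumption conflicts with the course the article itself expects.

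**Conclusion.** The point holds in conditional form. LOCF is a poor stated choice for this trial. The 6-month comparison is liable to bias, and neither its size nor its direction can be settled from the article. On adherence the plausible effect is modest: about 0.04 to 0.08 SD against SEEI under no effect with 20% against 10% loss (type I error about 6 to 8%), and a true 0.50 SD shrinking to about 0.44 with equal 15% loss if the effect grows over time. On function it is about 0.07 to 0.18 SD in favour of SEEI (type I error about 6 to 14%). The same rule could therefore understate the adherence benefit while overstating the functional one.

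These figures rest on assumed trajectories, dropout timing and loss by arm. Where low scorers were more likely to leave, the adherence bias under no effect was smaller. The documents do not support saying that the trial's result will be invalid. They support replacing the method while that is cheap.

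**What to change.** Replace LOCF as the main method with one of two approaches:

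- a likelihood-based mixed model for repeated measures on all observed scores, with group, visit, group by visit, baseline value and an unstructured covariance, which the MIXED procedure in SPSS 25 can fit; or
- multiple imputation.

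State that all randomised patients stay in the intent-to-treat set. A model restricted to patients with at least one follow-up would drop people whom the current rule retains. Baseline can instead be modelled as a response, or scores imputed for those with no follow-up.

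LOCF may be kept as a secondary analysis only. Both replacements assume data missing at random, so a sensitivity analysis of adherence under missing not at random is a useful optional addition.

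Cost: the planned repeated-measures MANOVA is replaced, which is more than a change of wording, and the analysis takes slightly more work. No new data or patients are needed. The change should be made before group allocation is revealed.
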